# Efficacy and safety of Hou Gu Mi Xi in patients with spleen qi deficiency syndrome who underwent radical gastrectomy for gastric cancer: protocol for a multicenter, randomized, double-blind, placebo-controlled trial

**DOI:** 10.1186/s13063-019-3429-x

**Published:** 2019-06-10

**Keywords:** Hou Gu Mi Xi, Randomized controlled trial, Traditional Chinese medicine, Gastric cancer, Radical gastrectomy, Spleen qi deficiency

## Abstract

**Background:**

Spleen qi deficiency (SQD), a syndrome based on traditional Chinese medicine (TCM) theory, is common in patients after radical gastrectomy. SQD manifests with chronic gastrointestinal disorders and systemic symptoms and is challenging to manage. Hou Gu Mi Xi (HGMX) is a dietary TCM formula for SQD. This study aims to evaluate the efficacy and safety of HGMX in patients with SQD who have undergone radical gastrectomy for gastric cancer.

**Methods and design:**

This study is a multicenter, randomized, double-blind, placebo-controlled trial. One hundred thirty patients with SQD who have undergone radical gastrectomy for gastric cancer will be assigned to receive either HGMX or placebo for 2 years. The main outcome will be changes in SQD symptoms assessed by the Spleen Qi Deficiency Symptoms Grading and Quantifying Scale. The secondary outcomes will be changes in quality of life assessed by the Short Form 36 scale, performance status as assessed by the Eastern Cooperative Oncology Group Performance Status scale, body weight, and body mass index. Progression-free survival will also be assessed as a secondary outcome. Adverse events (AEs), severe AEs, and study withdrawal due to AEs will be recorded to evaluate the safety of HGMX.

**Discussion:**

The results of this trial will provide initial evidence for the use of HGMX as an alternative and complementary intervention to manage chronic postoperative complications in patients who have undergone radical gastrectomy for gastric cancer.

**Trial registration:**

ClinicalTrials.gov, NCT03025152. Registered on 17 January 2017.

**Electronic supplementary material:**

The online version of this article (10.1186/s13063-019-3429-x) contains supplementary material, which is available to authorized users.

## Background

Although the incidence of gastric cancer is decreasing annually because of the popularization of *Helicobacter pylori* detection and eradication and improvements in living conditions, it represents one of the largest disease burdens worldwide [1]. According to the statistics reported by the World Health Organization in 2016, gastric cancer accounts for 1.53% of deaths worldwide, second only to lung cancer [2]. Due to the high *H. pylori* infection rate, dietary habits, and susceptibility genes, approximately 50% of gastric cancer cases worldwide occur in East Asian populations [3].

Radical gastrectomy, the standard treatment with a curative intent for patients with early-stage gastric cancer, can substantially prolong disease-free and overall survival [4]. However, chronic complications after the surgery and adjuvant chemoradiotherapy, such as chronic gastrointestinal disorders (e.g., abdominal distension and diarrhea) and general symptoms (e.g., physical fatigue and mental issue), are common and may lead to discomfort, malnutrition, hypoimmunity, decreased quality of life, and even cancer relapse [5]. Although the management of chronic complications is crucial for improving the prognosis of patients with gastric cancer, there are no specific interventions in the current guidelines for treating the complications except for surveillance and nutritional support [4, 6, 7]. Therefore, alternative and complementary therapies are popular in clinical practice [8, 9]; in particular, traditional Chinese medicine (TCM) is widely used to treat postgastrectomy complications in China, which has the heaviest disease burden of gastric cancer globally [10–12].

In TCM theory, the spleen (also written as “pi”, an abstract digestive organ in TCM that differs from the Western medical definition of the spleen as an immune organ) is responsible for transporting food and water, and qi is the vital life force produced by vital activity [13]. Patients who have undergone radical gastrectomy and chemoradiotherapy can easily suffer damage to the spleen and qi, leading to a spleen qi deficiency (SQD) syndrome, the typical symptoms of which include stomach and abdominal distension, dyspepsia, chest and stomach distress, borborygmus, diarrhea, fatigue, weakness, and weight loss [11, 14].

Dietary TCM therapy is a healthcare approach that penetrates Chinese people’s daily life. For example, people like eating medlar to tonify the kidney and liver and avoid contraindicated stimulating food (e.g., mutton, cock, and carp) to prevent the progression of inflammation or cancer. However, the efficacy of these dietary therapies is limited by their simple structure. Theoretically, dietary TCM formulas composed of multiple herbs will have a better efficacy than the simple forms.

Shen Ling Bai Zhu San, a classic TCM formula with the effects of invigorating the spleen and replenishing qi, has been validated to be effective and safe in treating SQD syndrome by empirical evidence for more than 3000 years [15]. It consists of *Renshen* (ginseng), *Fuling* (tuckahoe), *Baizhu* (atractylodes), *Yiyiren* (coixenolide), *Shanyao* (Chinese yam), *Lianzi* (lotus seed), *Sharen* (amomum), *Jiegen* (Platycodon), *Baibiandou* (white hyacinth bean), and *Gancao* (licorice), all of which are herbs that can be eaten as food (i.e., dietary herbs) except for *Baizhu*. Therefore*,* Shen Ling Bai Zhu San is appropriate for modification as a dietary TCM formula.

There is some evidence supporting the gastrointestinal protection and regulatory effects of Shen Ling Bai Zhu San. Animal studies have suggested that Shen Ling Bai Zhu San has the effects of regulating gut flora and increasing gastrointestinal motility [16]. A population-based survey from Taiwan showed that the number of Shen Ling Bai Zhu San prescriptions ranked fourth among all TCM formulas among 46,119 patients with gastric cancer and significantly decreased mortality in patients undergoing both total and partial gastrectomy during a 3.56-year median follow-up period [17]. A guideline developed by the Beijing Academy of Traditional Chinese Medicine recommends using Shen Ling Bai Zhu San as an adjuvant therapy for treating gastric cancer based on randomized controlled trial (RCT) evidence [18]. However, all RCTs supporting the efficacy of Shen Ling Bai Zhu San in the guidelines are of low quality.

A currently used dietary TCM formula called Hou Gu Mi Xi (HGMX) was developed by Jiangzhong Pharmaceutical (group) Co., Ltd. (Jiangxi, China), and is modified from Shen Ling Bai Zhu San. To modify the dietary formulation, HGMX does not contain *Baizhu*, which cannot be taken as a dietary supplement, and instead contains an alternative herb (*Jupi*) to maintain the main effects. As a result, all the herbs in HGMX can be used as both a drug and a dietary supplement according to the regulations in China. HGMX also increases the proportion of *Fuling*, *Yiyiren*, and *Baibiandou* to improve the effects of tonifying the spleen and dispelling dampness and decreases the proportion of *Renshen*, *Shanyao*, *Lianzi*, and *Gancao* because these herbs can cause dampness, which may affect the efficacy. The comparative components of HGMX and Shen Ling Bai Zhu San are presented in Table 1. In HGMX, *Renshen and Fuling* are the principal drugs, with *Renshen* having the main effects of tonifying qi and reinforcing the spleen and *Fuling* being responsible for dispelling dampness. *Yiyiren, Shanyao*, and *Lianzi* are used as adjuvant drugs to enhance the effects of the principal drugs, and *Sharen, Jiegen, Baibiandou, Gancao,* and *Jupi* help with the regulation and utilization of the entire formula. In addition, long-term patient compliance with Shen Ling Bai Zhu San is limited by the powder preparations and poor taste. To improve patient compliance, the HGMX preparation is changed from a powder to oatmeal by adding japonica rice and oats so that it can be brewed as a rice paste and conveniently eaten for breakfast. Japonica rice and oats also have slight effects of tonifying the spleen, which may enhance the efficacy of the herbs in HGMX.

**Table 1 Tab1:** Detailed components of Hou Gu Mi Xi and Shen Ling Bai Zhu San

Hou Gu Mi Xi			Shen Ling Bai Zhu San
Component	Part used	Proportion	Proportion
*Renshen* (ginseng)	Root	5.0%	12.9%
*Fuling* (tuckahoe)	Sclerotium	20.0%	12.9%
*Yiyiren* (coixenolide)	Seed	20.0%	6.5%
*Shanyao* (Chinese yam)	Root	10.0%	12.9%
*Lianzi* (lotus seed)	Fruit	10.0%	6.5%
*Sharen* (amomum)	Fruit	1.0%	6.5%
*Jiegen* (Platycodon)	Stem	5.0%	6.5%
*Baibiandou* (white hyacinth bean)	Seed	20.0%	9.7%
*Gancao* (licorice)	Stem	5.0%	12.9%
*Jupi* (orange peel)	Pericarp	5.0%	*Baizhu* (atractylodes) 12.9%

Every 30 g of Hou Gu Mi Xi contains an additional 13 g of early rice and 6.9 g of oats, in addition to 10.1 g of herbs

Based on TCM theory, we hypothesize that HGMX will be beneficial and safe for SQD syndrome caused by radical gastrectomy with better long-term patient compliance. However, because of the modifications, the RCT evidence for Shen Ling Bai Zhu San cannot be directly applied to HGMX, and furthermore, this evidence is not reliable. To evaluate the efficacy and safety of HGMX in patients with SQD and gastric cancer who have undergone radical gastrectomy, we plan to perform a 2-year randomized placebo-controlled trial (RCT). The results of this RCT will provide evidence for HGMX as an alternative and complementary therapy for the long-term management of chronic postgastrectomy complications.

## Methods/design

### Study design and recruitment

This study is a multicenter, randomized, double-blind, parallel, placebo-controlled trial. The flowchart of the study is presented in Fig. 1. The reporting of the protocol follows the Standard Protocol Items: Recommendations for Interventional Trials (SPIRIT) guidelines [19]. Additional file 2 contains the SPIRIT checklist. Four tertiary hospitals have agreed to participate in the trial, namely, the First Affiliated Hospital of Nanchang University, the Second Affiliated Hospital of Nanchang University, Jiangxi Hospital of Traditional Chinese Medicine, and Jiangxi Provincial Cancer Hospital.

**Fig. 1 Fig1:**
[figure not shown]
Flowchart of the study

The trial will recruit participants through Internet advertisements and posters in the hospitals. Patients who have undergone radical gastrectomy for gastric cancer and show interest in participating in the trial will be evaluated by an attending clinician to determine their eligibility. The clinician will inform the patient of the detailed study objectives, the study process, and the potential benefits and risks. All participants will sign an informed consent form prior to participation.

### Patient eligibility

An eligible patient should meet all of the following criteria:Age between 18 and 70 yearsPathological diagnosis of gastric cancerUnderwent radical gastrectomy, radiotherapy, chemotherapy, and treatment of surgical complications (such as leaks, strictures, and marginal ulcers) 2 weeks to 1 year previouslyFair performance status indicated by a score on the Eastern Cooperative Oncology Group (ECOG) questionnaire ≤1.Signed the informed consent formDiagnosed with SQD syndrome based on TCM theory as follows:Primary symptoms of spleen deficiency: (1) poor appetite, (2) stomach or abdominal distention, and (3) abnormal stools (loose stools or diarrhea)Primary symptoms of qi deficiency: (1) physical fatigue and weakness and (2) mental fatigue and taciturnitySecondary symptoms: (1) loss of taste or hypodipsia, (2) stomach or abdominal pain, (3) stomach tightness, (4) nausea or vomiting, (5) abnormal bowel sounds, (6) leanness or puffiness, (7) sallow complexion, (8) powerless defecation, and (9) facial or limb edemaAuxiliary symptoms: pale, swollen, or scalloped tongue with a thin and white coating.Patients who meet two primary symptoms of spleen deficiency plus two primary symptoms of qi deficiency, two primary symptoms of spleen deficiency plus one primary symptom of qi deficiency plus one auxiliary symptom, or one primary symptom of spleen deficiency plus one primary symptom of qi deficiency plus two secondary symptoms plus one auxiliary symptom will be diagnosed with SQD syndrome.

An eligible patient should not meet any of the following exclusion criteria:Stage IV gastric cancer according to the Japanese classification criteria [20]Completed radical gastrectomy, radiotherapy, and chemotherapy more than 1 year previouslyImpaired liver function (total bilirubin > 2 × upper limit of normal (ULN), alanine transaminase > 2 × ULN, or aspartate aminotransferase > 2 × ULN), kidney function (serum creatinine > 2 × ULN), or hematopoiesis (neutrophil count < 0.5 × 10^9^/L, thrombocyte count < 20 × 10^9^/L, or absolute reticulocyte count < 15 × 10^9^/L)Obviously abnormal electrocardiogramSevere mental disorderOther severe diseases (e.g., multiple organ failure or acquired immune deficiency syndrome)Pregnant or breastfeedingAllergy to the test sampleUnwilling to provide personal information.

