### Randomization and blinding

Eligible patients will be randomly assigned at a 1:1 ratio to receive either HGMX or placebo. We generated the random sequence using computer software. An independent randomization management center is responsible for sequentially assigning the random number and distributing trial samples to patients to ensure that the process of allocation is concealed. Clinicians, patients, data collectors, and outcome assessors will be blinded to the group assignment. The allocation will be unblinded if a severe adverse event occurs and when the final data analysis is complete.

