### Outcome measurements

#### Primary outcome

The primary outcome is the change in the total score of the Spleen Qi Deficiency Symptoms Grading and Quantifying scale (SQD scale). The SQD scale is a modified version of the classic scale for assessing the degree of SQD in the Clinical Guideline of New Drugs for Traditional Chinese Medicine [21]. The SQD scale consists of 17 items regarding symptoms of SQD: (1) stomach distension, (2) abdominal distension, (3) physical fatigue and weakness, (4) mental fatigue and taciturnity, (5) loss of appetite, (6) abnormal stools, (7) stomach pain, (8) stomach tightness, (9) abdominal pain, (10) acid reflux, (11) belching, (12) nausea and vomiting, (13) abnormal bowel sounds, (14) powerless defecation, (15) sallow complexion, (16) loss of taste and hypodipsia, and (17) facial and limb edema. Items 1–6 are the main symptoms; the other items are secondary symptoms. The items are assessed for duration (0–3 points, only available for items 1–2 and 7–9), severity (0–3 points, not available for item 13), frequency per day (0–4 points; 0–3 points for item 5), and frequency per week (0–5 points). The total score is the sum of the scores of each item (the main symptoms are scored twice) and ranges from 0 to 292. A higher score indicates a more severe symptom. Compared with the classic scale, we added four items (items 1, 7, 10, and 11), defined the main symptoms according to TCM theory, and assessed each item for duration, severity, and frequency per day and per week rather than only for severity. The details of the SQD scale are presented in Additional file 1.

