### Other assessments

Demographic profiles and histories of patients will be recorded at the baseline visit, including sex, age, marital status, education level, smoking and drinking habits, comorbidities, pathological type of gastric cancer, gastric cancer stage, type of resection surgery, chemoradiotherapy regimen, and medication history for the past 3 months.

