## Statistical analysis

Data analysis will be performed with Stata v14.0 (StataCorp LLC, College Station, TX, USA). The main primary outcome analysis will be based on the intention-to-treat data set, where the missing values will not be imputed and the patients who took unscheduled medications will be kept in their original group. We will also perform four sets of sensitivity analyses to test the robustness of the results of the main analyses, including (1) using the per protocol data set; (2) imputing missing data using various methods dependent on the proportion and distribution of the missing data; (3) excluding patients who become aware of the grouping accidentally during the trial, which also aims to estimate the placebo effects; and (4) excluding patients who took unscheduled medications. The analysis of secondary outcomes will be based on the per protocol data set, and the analysis of safety outcomes will be based on the safety data set only, both with no imputation. Interim data analyses will be performed after weeks 8 and 52.

Descriptive analysis will be conducted to explore the means and standard deviations of the continuous variables. We will assess the treatment effects by comparing the mean between-group differences of the continuous endpoints with a normal distribution using the independent *t* test. The skewed continuous variables will be described using medians and interquartile ranges. We will use the Mann-Whitney *U* test to assess the equivalency of the skewed continuous variable distributions. Moreover, we will describe categorical variables through their frequencies and percentages. We will evaluate the between-group differences using Pearson’s chi-square test for the cases with expected counts greater than 5 in more than 20% of cells and greater than 1 in any cell or Fisher’s exact test otherwise. We will perform subgroup analyses stratified by gastric cancer stage and chemoradiotherapy regimen for the primary outcome. We set α = 0.05 as the nominal type I error rate, which will be adjusted for the multiple *t* test using the O’Brien-Fleming group sequential method [25].

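### Patients may enter from 2 weeks to 1 year after treatment, yet the stated unadjusted comparison of change scores ignores that time and so gives up some precision

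*Protocol article*

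**What the plan says.** All references are to the protocol article.

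- **Patient eligibility.** Surgery, radiotherapy, chemotherapy and "treatment of surgical complications (such as leaks, strictures, and marginal ulcers) 2 weeks to 1 year" before entry are required. A matching exclusion removes patients who completed treatment more than a year earlier. The diagnosis of spleen qi deficiency sets no minimum symptom duration.
- **Primary outcome.** "The primary outcome is the change in the total score of the Spleen Qi Deficiency Symptoms Grading and Quantifying scale". The definition names no particular visit.
- **Randomization and blinding.** "Eligible patients will be randomly assigned at a 1:1 ratio to receive either HGMX or placebo"; no stratification factor is stated.
- **Other assessments.** The baseline items include "gastric cancer stage, type of resection surgery, chemoradiotherapy regimen, and medication history for the past 3 months". Time since surgery or since the end of treatment is not named, but the list is open-ended.
- **Statistical analysis.** Treatment effects are assessed by "comparing the mean between-group differences of the continuous endpoints with a normal distribution using the independent *t* test", with a Mann-Whitney test for skewed variables. "We will perform subgroup analyses stratified by gastric cancer stage and chemoradiotherapy regimen for the primary outcome". Four sets of sensitivity analyses are described, and none uses time since treatment.
- **Background.** The result is meant to inform "the long-term management of chronic postgastrectomy complications".

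**The concern.** The entry window spans a 26-fold range (2 to 52 weeks). Symptoms left by surgery or chemoradiotherapy may still be settling in a patient who enters early and may be stable in one who enters late. With change from baseline as the outcome, how much a patient improves without any active product plausibly depends on entry time. Two patients with the same baseline score at 3 and at 50 weeks may be on different courses, so the baseline score is only a partial substitute.

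An unadjusted test leaves that variation in the error term. The information needed to remove some of it is already at hand, because the eligibility criterion cannot be applied without treatment dates. What is at stake is the width of the confidence interval for the treatment difference. A secondary loss is that no stated analysis describes whether the effect varies with time since treatment, which bears on the intended use in chronic complications.

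**Working it through.** **Reproducing the plan's sample size.** Inputs from Sample size estimation: difference 8.0, SD 14.5, α 0.05, power 0.80, dropout 20%. Sidedness is not stated; two-sided reproduces the figure.

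n per arm = 2 × (1.960 + 0.842)² × 14.5² / 8² = 51.6, so 52. Then 52 / 0.8 = 65 per arm, 130 in total, which matches the article. With 52 evaluable per arm, SE = 14.5 × √(2/52) = 2.84 and power = Φ(8/2.84 − 1.96) = 0.80.

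**Assumptions not in the article.** It gives no recovery curve and no distribution of entry times. For illustration:
- entry time t is uniform over 2 to 52 weeks;
- a patient entering at t has a recoverable excess of E × exp(−(t−2)/13) points, with E = 10, 20 or 30;
- recovery by follow-up week f is that excess × (1 − exp(−f/13));
- the SD of 14.5 already contains this variation.

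**Spread of the recovery term.** For exp(−(t−2)/13) under uniform entry:
- mean = (13/50) × (1 − e^(−50/13)) = 0.254;
- mean square = (6.5/50) × (1 − e^(−100/13)) = 0.130;
- SD = √(0.1299 − 0.0647) = 0.255.

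The factor 1 − exp(−f/13) is 0.460 at week 8 and 0.982 at week 52. Recovery SD = E × 0.255 × factor; share = (recovery SD)² / 14.5²; adjusted SE = 2.84 × √(1 − share).

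| E | Week | Recovery SD | Share of 14.5² | Power after full adjustment |
|---|---|---|---|---|
| 10 | 8 | 1.2 | 0.7% | 80.6% |
| 20 | 8 | 2.3 | 2.6% | 81.4% |
| 30 | 8 | 3.5 | 5.9% | 82.6% |
| 10 | 52 | 2.5 | 3.0% | 81.5% |
| 20 | 52 | 5.0 | 12.0% | 85.0% |
| 30 | 52 | 7.5 | 26.9% | 90.8% |

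These are upper limits: they assume that the covariate captures the recovery term completely, and they credit none of it to the baseline score.

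**Chance imbalance.** With E = 30 at week 52, imbalance in recovery alone has a 95% range of ±1.96 × 7.5 × √(2/52) = ±2.9 points. The ordinary sampling error of the difference is ±1.96 × 2.84 = ±5.6 points and already contains it. Removing the recovery term narrows ±5.6 to about ±4.8.

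**What a subgroup could show.** Under uniform entry, (13 − 2)/50 = 22% of patients enter within 13 weeks of treatment, about 23 of 104 evaluable. A cut there gives an interaction SE of 14.5 × √(4/23 + 4/81) = 6.9 points. If the full 8-point effect were present in one group and absent in the other, power would be about 21%. Late entrants alone, about 40 per arm, would have about 70% power for an 8-point effect.

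**The case against.** The strongest reply is that nothing here is an error. The control is a concurrent, randomized, blinded placebo. Recovery happens in both arms, so the expected difference is unaffected, and an unadjusted t test is valid. Covariate adjustment is then an efficiency preference of a kind often settled in an analysis plan, which is not shown. This stands as far as validity goes. It does not dispose of the point, because the article does not leave the method open: it names a specific unadjusted test and two specific subgroup factors. The suggestion is an improvement on a stated choice.

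A second reply is that the size is wholly assumed. That also stands. An excess of 20 to 30 points is 2.5 to 3.75 times the planned effect, and at 10 points the gain is about one percentage point of power at either visit.

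A third concerns the baseline list. A reader might infer that time since treatment will not be recorded. The list is open-ended and eligibility requires the dates, so the text supports only that the variable is not listed and not used in any stated analysis.

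**Conclusion.** The point holds as a modest, nearly free gain in precision. Under the assumptions above, adjustment would lift power from 80% to at most about 81-83% at week 8 and 81-91% at week 52, part of which the baseline score would also deliver.

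Four stronger readings are tempting and are not supported:

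- **Bias.** Randomization against concurrent placebo removes it in expectation.
- **An underpowered trial.** If 14.5 excluded this variation, power would fall to about 78% when time since treatment explains 5% of the variance and to about 65% when it explains 30%. But 14.5 comes from the investigators' preliminary observational study and expert advice, and the article does not say which entry times that study covered. The SD may already include the variation, in which case the planned 80% stands.
- **Chance imbalance as an added threat.** The ±2.9 points are one component of the ±5.6 that the test already allows for.
- **Acute recovery mixed into a claim about chronic symptoms.** The criterion groups surgery, radiotherapy, chemotherapy and treatment of complications. A patient 2 weeks past the last of these may be months past surgery. By the week-52 visit even the earliest entrant is 54 weeks past treatment.

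**What to change.** - Derive weeks since last treatment, and weeks since surgery, for every patient from the dates already needed for eligibility. This includes the 80 patients enrolled when the article was submitted.
- Before unblinding, prespecify a linear model for the change in SQD score, with treatment, baseline SQD score and log weeks since last treatment, as the primary comparison in place of the unadjusted t test.
- Report a treatment-by-time interaction with time as a continuous term, labelled exploratory. Do not rest the main conclusion on late entrants: no cut-off is defined, and the interaction power shown above is low.

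The cost is one derived variable (two with time since surgery), a few model terms and one low-powered exploratory test. No extra visits or patients are needed.
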